#### Subgroup analysis

The primary analysis will be repeated including an interaction term between the treatment allocation and whether or not a patient received care in a hospital (outpatient appointment, day case, Accident and Emergency presentation or hospital admission) as a result of a fall in the 4 months prior to completion of the baseline questionnaire.

### Missing data

The amount of missing data will be reported by trial arm. A comparison of the baseline characteristics of participants who are included in the primary analysis will be undertaken to ensure that any attrition has not produced imbalance in the groups in important baseline covariates. A logistic regression model will be used to predict non-response (no falls data received postrandomisation) including all variables collected prior to randomisation. The primary analysis will then be repeated, including as covariates all variables found to be significantly predictive of non-response, to determine if these affect the parameter estimates and study conclusions.

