**Trial registration number:**

ISRCTN22202133; Pre-results.

Strengths and limitations of this studyThe largest randomised controlled trial in an English setting to assess the clinical and cost effectiveness of a home environmental assessment and modification for falls prevention.Investigates the feasibility of recruiting participants from databases of participants previously assembled while conducting cohort, falls prevention randomised controlled trials.Hosts three ‘Studies within a Trial’, which will add to the evidence base about recruitment strategies and ways to minimise missing data within trials.Results will be generalisable to a community-dwelling population of older people within England.Uses an unblinded, patient self-report primary outcome measure; therefore, there is a possibility of reporting bias.

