### Sample size

We propose to recruit and randomise 1299 participants to the OTIS trial in a 2:1 ratio (ie, 866 to usual care and 433 to intervention). This number allows for 10% attrition and provides 90% power (using two-sided significance at the 5% level) to show a difference in the percentage of participants who experience at least one fall in the 12 months following randomisation from 60% in the control group to 50% in the intervention group, accounting for the unequal randomisation (StataCorp. 2013. Stata Statistical Software: Release V.13). In the REFORM trial, previously conducted by some of the authors, an absolute difference of 5% was observed in the percentage of participants experiencing a fall (intervention group: 50%; control group: 55%), with a lower confidence limit of 13%; therefore, the decision was made to power this trial for a 10% absolute difference. In the event that sites are struggling with capacity to undertake assessments, we will consider using an allocation ratio of 3:1 (usual care to intervention) to reduce the number of participants they would have to see. If the final ratio was 3:1 (ie, 974 to the usual care and 325 to the intervention), we would have 85% power under the same conditions. The primary outcome is actually a count variable (number of falls, while proportion of participants experiencing at least one fall over the 12 months is a key secondary outcome); however, powering a trial for count data is more complex and requires greater assumptions and so a binary approach to the sample size calculation has been taken here.

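### The stated check on missing falls data selects covariates by significance and refits the same observed data, so it cannot show whether the conclusion survives outcome- or arm-dependent missingness

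*Protocol article*

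**What the plan says.** The Missing data section of the protocol article plans to report missingness by arm and to compare baseline characteristics of those analysed. It then fixes a two-step check.

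- Step 1: "A logistic regression model will be used to predict non-response (no falls data received postrandomisation) including all variables collected prior to randomisation".
- Step 2: the primary analysis is repeated, "including as covariates all variables found to be significantly predictive of non-response, to determine if these affect the parameter estimates and study conclusions".

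Three other places bear on this.

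- **Statistical analysis of the OTIS primary outcome.** The model is Poisson or negative binomial, adjusted for gender, age, fall history and allocation ratio, with months of returned calendars as exposure. The other analyses named there (therapist random effect, complier average causal effect) answer different questions.
- **Primary outcome measure.** Late calendars are chased by telephone or letter. Falls data from the 4-, 8- and 12-month questionnaires stand in where calendars are not returned.
- **Economic evaluation.** Multiple imputation is mentioned here, and not for the falls outcome.

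**The concern.** The stated aim of the check is to learn whether the study conclusions are affected. Two features of the method limit what it can say.

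First, a covariate enters only if it reaches significance in a model of complete non-response that holds every pre-randomisation variable. With few events and many candidates, true predictors are often missed and some noise variables get in. Whether a variable predicts falls plays no part, yet a variable unrelated to falls cannot correct bias in the fall rate.

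Second, the refit uses the same participants, counts and exposure term as the primary model. Both models assume that, given the covariates, a month without data has the same fall rate as a month with data. People with some calendars missing do not count as non-responders, so the first step never looks at them. If missingness depends on falls themselves, or does so differently by arm, the two fits will tend to agree and be wrong together. The trial is open and relies on self-report, so arm-dependent return of calendars is plausible. At stake is false reassurance about the primary rate ratio.

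**Working it through.** **1. The plan's own figures.** Inputs from Sample size: "from 60% in the control group to 50% in the intervention group", "using two-sided significance at the 5% level", 2:1 allocation; "This number allows for 10% attrition and provides 90% power".

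With k = 0.5 (intervention/control) and pooled p = (0.6 + 0.5 × 0.5)/1.5 = 0.567:

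n(control) = [1.96 × √(0.567 × 0.433 × 3) + 1.2816 × √(0.24 + 0.25/0.5)]² / 0.1² = 775.4, so 776. Intervention 388; total 1164; 1164/0.9 = 1293.3, so 1294 against the stated 1299. Power at 90% of 866 and 433 is 90.1%; at 90% of 974 and 325 it is 84.8% (stated 85%). The planning figures reproduce.

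**2. Events available to the non-response model.** At the 10% allowance, 1299 × 0.10 ≈ 130. The run-in (Trial design) and the strict definition of non-response both point to fewer. The number of candidate variables is not given; 20 to 40 is assumed.

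| Non-response (assumed below 10%) | Events | Events per variable, 20 | Events per variable, 40 |
|---|---|---|---|
| 10% | 130 | 6.5 | 3.2 |
| 5% | 65 | 3.2 | 1.6 |
| 3% | 39 | 1.9 | 1.0 |

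Null variables expected to pass at 5%: 20 × 0.05 = 1 to 40 × 0.05 = 2.

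Chance of selecting one true binary predictor (assumed odds ratio 1.5, prevalence 40%): P(|Z| > 1.96) with SE = 1/√(ev × (1 − ev/1299) × 0.4 × 0.6), ignoring correlation between predictors. This gives 0.17, 0.23, 0.35 and 0.57 at 26 (2%), 39, 65 and 130 events.

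**3. Does the refit detect outcome-dependent missingness?** Simulation under assumed settings: 300 runs, 1299 participants at 2:1, 30 baseline variables, negative binomial with dispersion 1, true rate ratio 1.00, all-or-nothing missingness.

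| Scenario | Full data | Primary | Refit | Rejections: full / primary / refit |
|---|---|---|---|---|
| (a) Missingness depends on covariates only | 1.00 | 1.00 | 1.00 | 4% / 5% / 6% |
| (b) Intervention participants with two or more falls more often missing (13% v 8% missing by arm) | 1.00 | 0.874 | 0.873 | 3% / 37% / 38% |

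In (b) the refit moved the log rate ratio by 0.0035 on average. The scenario is severe: in the intervention arm, the log odds of being missing were 2.0 higher with two or more falls than with fewer.

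**4. Size on the rate-ratio scale.** Assumed: control mean 1.5 falls, dispersion 1, which gives 1.5/(1 + 1.5) = 60% fallers and so matches the planning rate; observed ratio 0.80, hence intervention mean 1.2; 90% of each arm analysed (779 and 390); controls unchanged.

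SE(log RR) = √[(1/1.5 + 1)/779 + (1/1.2 + 1)/390] = 0.083

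Corrected RR = 0.80 × [(1 − m) + m × δ], where m is the share of months missing and δ the ratio of the missing to the observed rate in the intervention arm. CI = RR × exp(±1.96 × 0.083), with the SE held fixed.

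| m | δ | RR | 95% CI |
|---|---|---|---|
| – | 1 | 0.80 | 0.68–0.94 |
| 0.02 | 2 | 0.82 | 0.69–0.96 |
| 0.10 | 1.5 | 0.84 | 0.71–0.99 |
| 0.10 | 2 | 0.88 | 0.75–1.04 (upper limit 1.03 with the SE unrounded) |

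Tipping point at m = 0.10: 0.80 × exp(1.96 × 0.083) = 0.941; 1/0.941 = 1.062; δ = 1 + 0.062/0.10, about 1.6.

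**5. The planned effect on the same scale.** 50% fallers means μ/(1 + μ) = 0.5, so μ = 1.0 and the ratio is 1.0/1.5 = 0.67. SE = √[(1/1.5 + 1)/779 + (1/1.0 + 1)/390] = 0.085. At δ = 2: with m = 0.10, 0.73 (0.62–0.87); with m = 0.20, 0.80 (0.68–0.95). Both stay significant.

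**6. Cross-check on the binary planning scale.** 10% missing per arm (87 and 43), missing controls falling at 60%. An observed 7-point difference (z = 2.28) falls to z = 1.83 if 70% of the missing intervention participants fall. The full 10-point difference (z = 3.25) still gives z = 2.08 at 90% and is lost only near 100% (z = 1.74).

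**The case against.** The strongest case against has four parts.

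- **The analysis plan is not shown.** A departure from missing-at-random is commonly specified there. A reader might infer from the article that the trial has no such analysis at all; the documents do not support that. The point therefore rests on the method the article fixes and on the aim it gives that method.
- **The selection rule is inefficient, not harmful.** A reader might infer that chance-selected covariates distort the rate ratio. Nothing shows this. They are baseline variables in a randomised comparison; gender, age and fall history stay in regardless; and scenario (a) gives 1.00 for both fits. This stands.
- **An unreturned calendar need not be missing data.** Chasing and the questionnaires may recover falls, so the share of months truly missing may be well below 10%. At 2% missing and a doubled rate, 0.80 moves only to 0.82 and stays significant. Fewer non-responders weaken the selection model but also shrink the possible bias. This stands, and it limits what should be imputed.
- **The illustration needs strong assumptions.** The 0.80 is not a figure from the protocol, and significance is lost at twice the rate but not at 1.5 times. This also stands.

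It can further be said that the section does not claim to test non-random missingness. That is true of its wording, but judging the study conclusions is a wider aim than a refit within missing-at-random can serve.

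**Conclusion.** The concern holds in a limited form. The stated check selects covariates by an unreliable rule and repeats the primary model's assumption about unobserved months. Agreement between the two fits therefore says nothing about missingness that depends on falls or on arm.

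The effect is moderate. With 10% of months missing and controls unchanged, an observed 0.80 loses significance once missing intervention months run at about 1.6 times the observed rate. An effect of the planned size, about 0.67, survives a doubled rate even with 20% missing. A reader might infer that the planned effect is in danger; the figures do not support that. The issue matters for moderate or borderline results.

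These sizes rest on assumed values for the mean, dispersion, share of months missing and number of candidate variables. The argument that the refit stays within missing-at-random does not depend on them.

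The article also acknowledges that it "Uses an unblinded, patient self-report primary outcome measure; therefore, there is a possibility of reporting bias". Misreporting within returned calendars is a separate problem that this point does not cover.

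**What to change.** Make two changes, in the analysis plan if it does not already contain them.

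1. Replace significance selection with a pre-specified set of baseline predictors of falls and of non-response, entered whatever their p-values.
2. Add a delta-adjusted analysis of the primary outcome. Impute falls only for months still without falls data after chasing and questionnaire back-up, including months missing from partial returners. Use, for example, 0.5, 1, 1.5 and 2 times the expected rate, varied separately by arm, and report the tipping point at which the conclusion changes.

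The cost is some wording, a few hours of programming and one more sensitivity table. No new data are needed, and the primary analysis does not change.

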### Qualitative analysis

All interviews will be audio recorded digitally and transcribed verbatim. Initially, following familiarisation with the data, the interview material will be organised according to analytical headings using a constant comparison approach.^25^ Key themes will be identified that will then be contextualised in relation to the broader dataset and will be used to assist the interpretation of the trial result. For example, if the intervention is shown to be effective, we will use an Normalization Process Theory (NPT framework to facilitate the development of an implementation plan for integration of occupational therapy falls environmental assessment into routine practice. During the analysis, regular meetings will be held between the qualitative research team and project steering group to discuss emergent themes.

### AE data

AE data will be summarised descriptively by randomised arm.

### Trial monitoring

A Trial Steering Committee and Data Monitoring and Ethics Committee will monitor the trial at least every 12 months or more frequently if the committee requests. The role of this committee will include the review of all SAEs that are thought to be treatment related and unexpected.

### Economic evaluation

The health economic evaluation aims to establish the cost-effectiveness of OT delivered environmental assessment and modification in terms of preventing falls and assess the impact of the intervention on participants’ quality of life. The economic analysis will be performed using individual patient level data on an ITT basis. The analytical approach will take the form of cost-effectiveness and cost–utility analyses. The cost-effectiveness approach will assess value for money in terms of cost per fall averted, and the cost–utility analysis will assess cost per quality-adjusted life-year (QALY) gained. The perspective for both analyses will be that of the UK NHS and personal social services, as well as secondary analyses undertaken from a societal perspective. Discounting for future cost and health benefit will not be undertaken given the time frame for the trial is 12 months after randomisation. The year of pricing will be set as the mid-year of the trial.

Health benefits associated with the treatments will be measured in terms of both estimates of the mean number of falls, corresponding to the main outcome of the trial, and mean QALYs, defined as a year lived with full health. In line with NICE recommendations,^26^ the EuroQol EQ-5D^27^ will be used to elicit patient utility values at different points in time and used to calculate QALYs for each patient, using the area under the curve approach.^28 29^ These utility values are used as ‘quality adjustment’ for each patient’s survival time. Specifically, the EuroQol EQ-5D-5L will be used.

Cost data will be collected for each patient regarding healthcare resource use, specifically within primary care and the community (ie, GP, nurse, physiotherapist and OT visits) and the hospital setting (ie, outpatient attendances, day cases, inpatient stays and accident and emergency attendances). Unit costs will then be applied to estimate the total cost per patient. Additional information will be collected regarding intervention costs and private/personal expenses that feed into the societal perspective analysis (eg, activities of daily living equipment and travel costs for healthcare attendances). Unit costs will be obtained from established costing sources such as NHS Reference Costs^30^ and PSSRU Unit Costs of Health and Social Care.^31^ Data on the cost and utility measures will be collected prospectively at baseline, 4, 8 and 12 months via self-reported questionnaires.

Mean within-trial estimates of cost and health benefits will be estimated using regression methods, allowing for the correlation between costs and effects, as well as adjusting for covariates. The results will be presented as incremental cost-effectiveness ratios, where the difference in mean cost estimates between the two arms is divided by the difference in mean health benefit between the two arms. Findings will also be presented in terms of net health benefit.^32^ Multiple imputation methods will be used to handle missing data where needed.^33^

The uncertainty surrounding the decision to accept a treatment as the most cost-effective will be explored in cost-effectiveness acceptability curves (CEACs).^34^ These curves depict the probability of accepting a treatment as being cost-effective for a large range of willingness to pay values for an extra unit of health benefit. Sensitivity analysis will be conducted to explore the impact of underlying assumptions of the analysis and the range of unit costs on the cost-effectiveness results.

The main outcome of the trial, falls reduction, is associated with a reduction in fractures. However, due to the restriction in the length of follow-up, the long-term effect in terms of the decreasing number of fractures might not be observed in the current trial. Therefore, a further analysis will explore the possible long-term impact of the trial, assuming that a falls reduction should also lead to a fracture reduction. A decision analytic model approach will be adopted to perform this task. The perspective will be the UK NHS and personal social services, with a lifetime time horizon whereby every participant in a hypothetical cohort is followed up until the last participant dies. The hypothetical cohort will be constructed, based on the characteristics of the trial population, to estimate the QALY yield and cost saving of the long-term effect of the intervention. The model parameters that are not collected in the trial will be extracted from the existing literature.

The model outputs will be the estimated expected mean costs, effectiveness and QALYs associated with each alternative treatment. Estimated total costs and outcomes will be discounted according to the latest health technology appraisal guidance.^26^ Uncertainty regarding cost-effectiveness will be evaluated using probabilistic sensitivity analysis, where inputs into the analysis are defined as probability distributions that reflect uncertainty.^35^ The uncertainty surrounding the decision to adopt a given treatment option as a cost-effective treatment at different levels of willingness to pay will be represented in CEACs. The impact of assumptions undertaken in the analysis regarding the evidence over parameters or relating to the decision model (such as extrapolation) will be evaluated in sensitivity analysis, if possible.

## Patient and public involvement statement

Our patient representatives were identified from the cohort of participants who have taken part in previous studies run the members of the study team. They helped develop the design and conduct of the study by providing feedback on the grant application submitted to the funder. We have set up a Patient Involvement Group. This group gives advice to the trial team on the design and conduct of the trial. This included providing input into case report forms, information sheets, participant newsletters and recruitment strategies. They have agreed to help us disseminate our research findings by providing assistance with writing the plain language summaries and the research study findings letter we will send to participants who request it. A member of the group is also a member of the Trial Steering/Data Monitoring and Ethics Committee, where PPI is a standing item.

### Studies within trials

In addition to the main OTIS study, three ‘Studies within a Trial’ (SWATS) are being conducted.

### Pen substudy

The aim of this substudy is to evaluate the effectiveness of including a pen with the trial invitation pack on recruitment of participants to the OTIS study. Any patient identified in the GP mail out as eligible to receive an OTIS trial invitation pack will be entered into the pen substudy. Block randomisation will be used to allocate participants in a 2:1 ratio in favour of the control group. Generation of the allocation sequence will be undertaken independently by a researcher not involved with the production of the recruitment packs. A single block the size of the number of participants from each GP practice will be used. The intervention group will receive a pen with the YTU logo/details on it; the control group will not receive a pen at the point of being invited to take part in the study. The primary outcome is the proportion of participants who go on to be randomised to the OTIS trial. Secondary outcomes include: the proportion of participants who return a screening form; time to return screening form; the proportion of participants who fulfil the eligibility criteria apart from the criterion relating to falls within past 12 months or fear of falling; the proportion of participants who are eligible for randomisation; and the proportion of participants who remain in the trial at 3 months postrandomisation. Categorical data will be compared using logistic regression and time to response via a Cox proportional hazards model.

### Invitation letter substudy

The aim of this substudy is to evaluate the effectiveness of writing the potential participant’s name by hand on the invitation letter, versus printing their name, on the recruitment rate to the study. Participants will be eligible for this substudy if are they due to be sent an invitation pack about the OTIS trial in the first mail out undertaken by the Yorkshire Health Study. Block randomisation will be used to allocate participants in a 1:1 ratio to receive either a hand written name on the invitation letter (intervention group) or printed name on the invitation letter (control group). Generation of the allocation sequence will be undertaken independently by a researcher not involved with the production of the recruitment packs. The primary outcome is the proportion of participants who go on to be randomised to the OTIS trial. Secondary outcomes include: the proportion of participants who return a screening form; time to return screening form; the proportion of participants who fulfil the eligibility criteria apart from the criterion relating to falls within past 12 months or fear of falling; the proportion of participants who are eligible for randomisation; and the proportion of participants who remain in the trial at 3 months postrandomisation. Categorical data will be compared using logistic regression and time to response via a Cox proportional hazards model.

### Text message substudy

The aim of this substudy is to evaluate the effectiveness of a personalised text message compared with a standard text message on postal questionnaire response rates. Participants who are due to be sent their 4-month follow-up questionnaire and who have provided a mobile phone number and consented to be contacted by text message will be randomised. Block randomisation will be used to allocate participants in a 1:1 ratio to receive either a personalised (intervention group) or a standard text message (control group) at the same time as they are due to receive their postal follow-up questionnaire (ie, 2–4 days after the questionnaire is sent). The randomisation will be stratified by main trial allocation. Generation of the allocation sequence will be undertaken independently by a researcher not involved with the delivery of the text messages.

The personalised text message will read, ‘*OTIS Trial: [Title, surname of participant] you should have received a questionnaire in the post by now. Your answers are important; so please help by returning it as soon as you can. Thanks.*’.

The standard text message will read ‘*OTIS Trial: you should have received a questionnaire in the post by now. Your answers are important; so please help by returning it as soon as you can. Thanks*.’. The primary outcome is the proportion of participants in each group who return the questionnaire. Secondary outcomes include time to response, completeness of response, whether a reminder notice is required and cost-effectiveness. Categorical data will be compared using logistic regression and time to response via a Cox proportional hazards model. All models will adjust for main trial allocation.

